### Intervention

2.6

All participants will receive 25 minutes of robot-assisted therapy with the ArmeoPower device (Hocoma, Volketswil, Switzerland), daily on weekdays for 2 weeks, for a total of 10 sessions. The robot-assisted therapy will be managed by the same experienced occupational therapist who will choose the adequate program for each participant. According to the participant's group allocation, anodal tDCS or sham tDCS will be applied concurrently with the robot-assisted therapy. The experimental setup is demonstrated in Figure 2. The time used to adjust the tDCS setup and the robotic arm will not be counted as therapy time. All subjects will undergo an additional 30 minutes of conventional occupational therapy and will be permitted to engage in physical therapy to restore gait during the intervention period. Intervention will be halted at any time, on the participant's request or on the primary investigator's decision, upon any severe adverse events.

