#### Primary outcome

2.8.1

The primary outcome is the change in FMA-UE scores between T0 and T1. The FMA-UE is a quantitative measure of motor impairment of the upper extremities, ranging from 0 to 66, with higher scores indicating less motor impairment.^[24]^

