#### Secondary outcomes

2.8.2

Secondary outcomes are the change in FMA-UE scores between T0 and T2, and the changes in mRS scores, K-MBI scores, Brunnstrom stages, BBT scores, MAS scores of the wrist flexor/extensor, elbow flexor/extensor, and finger flexor, MRC Scale scores of shoulder abduction, elbow flexion/extension, wrist flexion/extension, and finger flexion/extension between T0 and T1 and between T0 and T2, as well as the change in the EEG LI between T0 and T1.

The mRS is a categorical measure of disability incorporating mental and physical status after neurological deficits. The scale consists of 6 grades, from 0 (no symptom at all) to 5 (severe disability), and 6 (death).^[25]^ The K-MBI is the Korean version of the MBI, which measures the degree of independence of ADL according to 10 items, with the total score ranging from 0 (completely dependent) to 100 (independent).^[26]^ The Brunnstrom stage is the motor recovery stages after stroke, with the recovery process classified into six stages from 1 (flaccidity with no movements of the limbs) to 6 (individual joint movements).^[27]^ The BBT is a measure of gross manual dexterity, assessed by counting the number of blocks moved from one compartment to another across the partition in 60 seconds, with proven validity.^[28]^ The MRC is an ordinal scale of muscle power, with proven reliability, and the MAS is a scale of spasticity which is graded from 0 to 4, larger numbers indicating more increased resistance to passive movement of the joints.^[29,30]^

The EEG LI will be calculated to measure the lateralization of cortical activity during rest and task performance. LI is calculated as LI = (NL-NR)/(NL+NR), and values range between −1 and 1. An LI > 0.2 indicates a predominance of right cerebral cortical activity, an LI < −0.2 indicates predominance of left cerebral cortical activity, and an LI between −0.2 and 0.2 is considered “not lateralized.”^[31]^

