### Sample size

2.10

The clinically important difference for the FMA regarding participants’ ability to move their arm has been reported as 9 to 10.^[32]^ A previous study on anodal tDCS or sham tDCS in patients with stroke revealed a standard deviation of 10.^[33]^ When estimating the drop-out rate as 10%, with a power of 80% at a 2-tailed significance level of 5%, the total required sample size is 36, that is 18 participants in each group.

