### Statistical analysis

2.12

The primary analysis will be done on a modified intention-to-treat (ITT) population of participants who were randomly assigned to groups and underwent >1 therapy session. Participants who complete the 10 tDCS sessions and all 3 (T0, T1, and T2) assessments per protocol will be included for the secondary endpoint analysis to verify a sustained clinical response. For between-group comparisons of baseline characteristics, Student *t* tests or Mann–Whitney *U* tests for continuous variables and *χ*^2^ tests or Fisher exact test for categorical variables, depending on normality, will be used. Student *t* tests or Mann–Whitney *U* tests will be performed to investigate if the changes in primary and secondary outcome measures are different between the anodal tDCS and sham group. All statistical analyses will be performed using SPSS (version 25.0), and *P* values <.05 will be considered statistically significant. In the repeated measures analysis including assessments of T2, Bonferroni correction will be applied and the significance level will thus be adjusted to 0.05/2 = 0.025.

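### The T2 sustained-response analysis is confined to full completers, a subset of the primary population selected after randomisation

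*Protocol article*

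**What the plan says.** Section 2.12 (Statistical analysis) names two populations in consecutive sentences.

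- The primary analysis uses a "modified intention-to-treat (ITT) population of participants who were randomly assigned to groups and underwent >1 therapy session".
- The next sentence restricts the set: "Participants who complete the 10 tDCS sessions and all 3 (T0, T1, and T2) assessments per protocol will be included", and gives its purpose: "for the secondary endpoint analysis to verify a sustained clinical response".

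The endpoints to which these apply are in section 2.8. For the primary, "The primary outcome is the change in FMA-UE scores between T0 and T1". For durability, "Secondary outcomes are the change in FMA-UE scores between T0 and T2", followed by the other scales at T1 and T2.

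Section 2.6 (Intervention) shows how a participant can fail to complete: "Intervention will be halted at any time, on the participant's request or on the primary investigator's decision, upon any severe adverse events".

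Section 2.12 also sets a significance level of 0.025 for analyses that include T2. The article states no modified ITT analysis of T2 and gives the completer set no supporting or sensitivity role.

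**The concern.** Completing ten sessions and three visits is something that happens after allocation. Participants may stop at their own request or by the investigator's decision, and either can in principle differ between active and sham stimulation and be related to how the arm is recovering. Once the comparison is conditioned on completion, randomisation no longer guarantees that the groups being compared are alike.

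Two further consequences follow from the rule as written.

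- It discards usable data. T0–T2 change needs only T0 and T2. Someone with both values is excluded for an incomplete session count or a missed T1 visit.
- It weakens the stated purpose. Sustained response is a statement about whether the T1 effect is still there at T2. With T1 analysed on one set and T2 on a subset of it, a change in the estimate can reflect who was dropped as well as what happened over time.

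At stake is the interpretation of the trial's evidence on durability, not its primary result.

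**Working it through.** **1. Reproduce the planned sample size (section 2.10).** Inputs: a clinically important difference that "has been reported as 9 to 10", SD 10, power 80%, two-sided 5%, and drop-out of 10%.

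- Normal approximation with difference 10: n per arm = 2 × (1.960 + 0.842)² × (10/10)² = 15.7, so 16.
- Inflated for drop-out: 16 / 0.90 = 17.8, so 18 per arm and 36 in total. This matches the article.
- With difference 9 the same steps give 20, then 23 per arm (46 in total), so the stated 36 rests on the upper end of the range. The t-based version at difference 10 gives 17, then 19 per arm.

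**2. Participants expected at T2.** With 10% drop-out, 18 × 0.90 = 16.2, so about 16 per arm. This is the fair reference for any analysis of observed T2 values. A participant with no T2 measurement contributes no observed T2 change under either population.

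**3. Power at the T2 level.** Two-sample t-test, two-sided 0.025, non-centrality = (difference/SD) × √(n/2), degrees of freedom 2n − 2. It is assumed that the difference and SD of section 2.10 also hold for T0–T2 change.

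| n per arm | Power, difference 10 | Power, difference 9 |
|---|---|---|
| 18 (no loss at all) | 0.741 | 0.640 |
| 16 (planned drop-out) | 0.680 | 0.578 |
| 15 (one more per arm removed, assumed) | 0.646 | 0.545 |

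The cost attributable to the completer rule is the step from 16 to 15: 0.680 − 0.646 = 0.034 at difference 10, and 0.578 − 0.545 = 0.033 at difference 9. That is about 3 percentage points per additional exclusion in each arm.

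**4. Possible bias.** None of the following assumptions is in the document: no true effect, SD 10, 18 per arm, non-completers removed from one arm only, and correlation ρ between outcome and the tendency to complete. When a fraction q is removed, the mean of those who remain shifts by approximately

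shift = SD × ρ × φ(z_q) / (1 − q).

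For q = 0.10, φ(1.282)/0.90 = 0.195, so the shift is 0.58 at ρ = 0.3 and 0.97 at ρ = 0.5. Simulation with whole participants (20,000 trials per scenario) gives:

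| Removed from one arm | ρ | Spurious difference (points) | Rejection rate at nominal 0.025 |
|---|---|---|---|
| 2 of 18 | 0 | about 0 | 0.023 |
| 2 of 18 | 0.3 | 0.6 | 0.026 |
| 2 of 18 | 0.5 | 1.0 | 0.034 |
| 2 of 18 | 0.8 | 1.6 | 0.047 |
| 4 of 18 | 0 | about 0 | 0.025 |
| 4 of 18 | 0.3 | 1.1 | 0.032 |
| 4 of 18 | 0.5 | 1.8 | 0.046 |
| 4 of 18 | 0.8 | 2.9 | 0.084 |

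Near the planned drop-out the distortion is small unless completion is strongly tied to outcome, and it grows with non-completion. The sign depends on which arm loses participants and on whether those lost are doing worse or better than the rest.

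**The case against.** The strongest reply is that T2 is secondary, the completer set is openly described as per protocol, and the primary comparison is untouched. All of that is true, and it limits the importance of the point. It does not remove it: the article assigns the sustained-response question to this set alone, so this is a stated choice and not a detail left to a document that is not shown.

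Several stronger readings are tempting, and the article does not support them.

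- *The rule costs about nine points of power (74% to 65%).* A reader could get this by setting 15 per arm against 18. But section 2.10 budgets for loss ("When estimating the drop-out rate as 10" per cent), so 18 observed T2 values per arm were never expected. The fair contrast is 68% to 65%, and the drop to 15 is itself assumed.
- *T1 and T2 are assessed in different patients.* Completers are a subset of the modified ITT set, and with the planned drop-out most participants would be in both.
- *The T2 estimate will be inflated in favour of tDCS.* This needs losses concentrated among poor responders in the active arm. In a double-blind trial whose sham uses the same configuration with 30 seconds of current, one-sided loss cannot be presumed.
- *The T0–T1 secondary outcomes are also limited to completers.* The sentence ties the set to sustained response. Wider use is possible but not established.
- *Participants who stop sessions are not followed.* Section 2.6 halts the intervention, not assessment, and section 2.7 schedules the visits without a completion condition.

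The article also does not say whether missed sessions can be made up, so how many participants the ten-session condition would remove is unknown.

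**Conclusion.** The point holds as a weakness in the choice of population for the T2 analysis. The article makes the durability comparison in a subset defined by events after randomisation, and excludes participants whose T2 was measured.

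The consequence is real but moderate. Bias is unknown in size and direction: nil if completion is unrelated to outcome, and 0.6 to 1.6 FMA-UE points if 2 of 18 are lost from one arm only with ρ between 0.3 and 0.8. The power loss is about 3 percentage points if one further participant per arm is removed beyond the planned drop-out. These figures rest on the assumed scenarios and on carrying the SD and difference of section 2.10 over to T2. The T0–T1 primary conclusion and the planned total of 36 are unaffected. The change is worth making because it is nearly free, not because the damage is shown to be large.

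**What to change.** In section 2.12, state that the main analysis of T0–T2 change uses the same modified ITT population as the primary analysis and includes every observed T2 value, whatever the number of sessions completed and whether or not T1 was missed. The between-group tests already planned are sufficient for this. A mixed model for repeated measures is one option, not a requirement. Keep the analysis of participants with all ten sessions and all three assessments, labelled as a sensitivity analysis. In the same edit, say which population applies to the T0–T1 secondary outcomes, since the present wording leaves that open.

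The cost is a change of wording and slightly more analysis work. The planned enrolment, treatment and visit schedule stay as they are. The T2 estimate may turn out less favourable than in completers. Recruitment was still ongoing when the article was submitted (section 2.2). If the change is made before unblinding, it cannot be influenced by the results.

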## Discussion

3

This study aims primarily to investigate the effects of anodal tDCS over the contralesional premotor cortex in patients with subacute stroke with severe upper extremity hemiparesis. Under the concept of IHI model, contralesional cathodal tDCS has been used with conflicting results. Therefore, another model called “bimodal balance-recovery model” is introduced highlighting ∼ the promotion of contralesional cortex function in stroke with severe motor impairment. This will be the first randomized controlled trial investigating the effect of contralesional anodal tDCS in patients with subacute stroke with severe upper extremity motor impairments. The expected results will be better outcome measure improvements in anodal tDCS group than sham tDCS group. Secondarily, the EEG signals are collected to further investigate neurophysiological markers to predict responders or nonresponders for this new tDCS protocol. Results of this study will help to establish a new EEG signal-based precise tDCS protocols for stroke patients with severe motor impairment.
